#### Primary outcome measure

Our primary outcome will be the cardiorespiratory fitness expressed as pVO2 during a graded maximal CPET on a bicycle until exhaustion (JAEGER Vyntus CPX, Vyaire medical, USA). pVO2 is determined as the highest attained peak VO2 during an average of 30 s of exercise. We choose pVO2 as our primary outcome because it has been shown to be the most important independent predictor of CV morbidity and mortality in patients with HFpEF stage A–C (28). A 5 + 5 W/min, 10 + 10 W/min, 20 + 20 W/min, or 50 + 25 W/min continuous ramp protocol will be used according to the participants’ estimated fitness level to ensure a CPET duration between the recommended 8–12 min (29). A 12-lead electrocardiogram will be monitored continuously, and gas exchange will be measured breath-by-breath. Blood pressure will be measured automatically every 2 min (SunTech Tango M2, SunTech Medical, USA). After reaching maximal exertion, the patients will cycle another 3 min to measure recovery heart rate, blood pressure, rating of perceived exertion and to document the reason for test termination. All raw CPET data will be forwarded for analysis to a blinded CPET core lab at KU Leuven to ensure reliable analysis of the data.

#### Secondary outcome measures

##### Physical activity

A validated tri-axial accelerometer (ActiGraph™ GT9X Link, ActiGraph LLC, Pensacola, Florida, USA) will be used to objectively measure the patient’s physical activity level (30). Participants will be asked to wear the ActiGraph GT9X Link on the non-dominant wrist for 24 h/day for 7 days. Measurements will be considered valid when at least 3 weekdays and 1 weekend-day of 10 h wear-time have been recorded (31). ActiLife software will be used to extract the raw data from the physical activity monitor which will then be transferred to the physical activity core lab at KU Leuven for offline analysis. The following parameters will be determined: number of steps (key secondary outcome), energy expenditure (total and active), time spent doing MVPA (key secondary outcome) and number of sedentary bouts.

##### Muscular fitness

A maximal voluntary isometric handgrip strength test will be performed using a JAMAR dynamometer (JLW Instruments, Chicago, Illinois, USA) (32). For each hand, the patient will perform three repetitions while sitting upright on a chair and with the elbow at 90° flexion. The maximum value (in kg) for each hand will be recorded. Additionally, muscle strength and endurance of the quadriceps muscle will be tested in the right leg using a Biodex system 3 Pro (Biodex Medical Systems Inc., Shirley, New York, USA) (33). Patients will be instructed to perform three voluntary maximal isometric quadriceps contractions for 6 s, interspersed with a 1 min rest period. The highest value will be used in the analysis as a measure of isometric power. This will be followed by two bouts of 25 repetitive maximal isokinetic knee extension-flexion movements interspersed with a 2 min recovery period.

##### Body Composition

Body composition will be measured in the supine position using Bodystat 1,500 (Bodystat Ltd, Douglas, Isle of Man, UK) (28). Anthropometric characteristics such as length (stadiometer) and body mass will be measured to the nearest 0.1 cm and 0.1 kg in fasting state and light clothing to calculate body mass index (kg/m²). Waist circumference is measured using non-elastic tape.

##### Blood biochemistry

A blood sample will be drawn with the patient in a fasting state and biochemical analysis includes fasting glucose, hemoglobin A1c, total cholesterol, low-density lipoprotein cholesterol (LDL-C), high-density lipoprotein cholesterol (HDL-C), triglycerides, creatinine and NT-proBNP.

##### Rest transthoracic echocardiography

Comprehensive two- and three-dimensional echocardiography will be performed by experienced sonographers using a standardized protocol (see Supplementary File S2). All recordings will include at least 3 cardiac cycles and qualified readers will interpret the images offline using EchoPAC software (version 204, GE Vingmed, Horten, Norway). The standard protocol will include conventional cardiac dimensions, mass, and systolic and diastolic function in accordance with contemporary international guidelines (34, 35).

*Exercise echocardiography combined with CPET (CPET-echo)* will be performed following a standardized protocol as described before (see Supplementary File S2) (36–40). Exercise will be performed on a semi-supine bicycle ergometer (Ergoline GmbH, Bitz, Germany) with a continuous ramp protocol aiming for a total exercise duration of 10–12 min (60–65 rotations/min). Images will be acquired at rest, low intensity (HR between 90 and 100 beats per min, before fusion of E and A waves, or at an RER between 0.85 and 0.9 when chronotropic incompetence is present), and at peak exercise (RER >1.05). Loop registration of at least 10 beats will be made to overcome the expected decrease in acoustic quality caused by hyperventilation. At one year of follow-up, the CPET-echo will follow the same imaging protocol. The power output at low-intensity exercise will be identical to the low-intensity workload during the baseline CPET-echo at the time of inclusion. In contrast, the power output of the peak exercise stage will be determined based on the criterion of achieving RER 1.05. All analysis will be performed offline at the core lab of Leuven using EchoPAC software (version 204, GE Vingmed) in accordance with contemporary international guidelines (34, 35).

*Health-related quality of life (HRQoL)* will be assessed via the generic RAND-36 Questionnaire (SF-36), administered as an online survey via the web-based application REDCap (41). Here, different components are addressed: physical functioning (10 items), limitation due to physical health (4 items) or emotional problems (3 items), energy and fatigue (4 items), emotional well-being (5 items), social functioning (2 items), pain (2 items), general health (5 items) and perceived change in general health (1 item). All items are scored on a nominal or ordinal scale and transformed to a percentage of impairment (0% complete impairment, 100% no impairment). In addition, the EQ-5D-5l questionnaire will be administered covering five dimensions: mobility, self-care, usual activities, pain/discomfort and anxiety/depression. The health status profile can be translated into a utility value between 0 and 1, serving as input for the health economic evaluation.

##### Safety

Adverse events will be monitored for 2 years after randomization. All adverse events will be recorded and reported in accordance with the Good Clinical Practice decision tree for adverse event reporting and will be reported to the central research ethics committee. Serious adverse events (SAE) are defined as all-cause mortality, hospitalization for CVD or serious atrial or ventricular arrhythmia. Other adverse events will include training-related adverse events such as muscle, tendon or joint problems that will preclude exercise participation or other diseases that require an interruption of the exercise intervention.

*Implementation potential* will be evaluated by measuring adherence [defined as a % of recommended duration of exercise (minutes)] and compliance [will be calculated as % of time at the recommended intensity (i.e., within correct heart rate zone)] to the exercise intervention. These data will be collected using the GARMIN sports watch or exercise diary for those patients encountering difficulties using the watch. In addition, the usability and feasibility of PRIORITY will further be assessed using the Users Experience Questionnaire (UEQ) and the System Usability Scale (SUS) (42).

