#### Comparator group

Patients randomized to the comparator group will be advised to be physically active and will receive a personalized exercise prescription as automatically generated by the EXPERT tool and orally explained to the patient (26). Subsequently, patients are free to participate in any form of physical activity or structured exercise. However, there will be no contact between the patients and the investigators to provide feedback or support during the 1-year FU period, except for the four-month FU assessment.

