##### From year one to year two

As shown in Figure 2, all patients will receive an overview of the change of their physical fitness test results one year after their baseline measurements. Patients in the PRIORITY group will then be invited for four physical activity consultations: immediately at month 12 and then subsequently at month 15, month 18 and month 21 to discuss their current physical activity behaviour and further co-design their physical activity program addressing barriers and enablers of physical activity. The key component of the physical activity intervention consists of motivational interviewing to evoke intrinsic motivation to support long-term behavioural change. Patients of the PRIORITY group will still be able to make use of the web-based exercise platform, their resistance training bands, their sports watch and chest strap. Patients with HFpEF stage C will also keep their home-ergometer. Patients in the comparator group will not be contacted during this year.

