	*Quality of life* via *EQ-5D-5l questionnaire*	X	X	X	X
Safety monitoring	Adverse events reporting by patients	X——————––X			
Other outcomes					
Sociodemographic characteristics	General Questionnaire	X	X	X	X
Substudy: muscle metabolism	Device for muscle oxygenation measurements (PortaMon)	X		X	
Substudy: vasoreactivity/vasomotor function	Flow mediated slowing via Vicorder	X		X	

T0, baseline; T1, measurement at 4 months; T2, measurements at 1 year; T3 measurements at 2 years; NIRS, near infrared spectroscopy; FMS, flow mediated slowing.

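### The SAE list leaves out non-cardiovascular hospitalisation, and adverse-event counts by arm are at risk of unequal ascertainment

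*Protocol article*

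**What the plan says.** All of the event definitions are in the Safety section of the protocol article.

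- Period: "Adverse events will be monitored for 2 years after randomization".
- Recording rule: "All adverse events will be recorded and reported in accordance with the Good Clinical Practice decision tree for adverse event reporting".
- Serious events: "Serious adverse events (SAE) are defined as all-cause mortality, hospitalization for CVD or serious atrial or ventricular arrhythmia".
- Non-serious events, first kind: "Other adverse events will include training-related adverse events such as muscle, tendon or joint problems that will preclude exercise participation".
- Non-serious events, second kind, which concerns illness and not injury: "other diseases that require an interruption of the exercise intervention".

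Table 3 gives the source as "Adverse events reporting by patients", drawn as a continuous line and not as visit-by-visit crosses.

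The contact schedule differs by arm. PRIORITY patients have 18 supervised sessions in year 1 and four physical activity consultations from month 12 to month 21. They are also contacted if six prescribed home sessions in a row are missed. For the comparator in year 1, "there will be no contact between the patients and the investigators to provide feedback or support during the 1-year FU period", with the 4-month assessment as the stated exception. For year 2, "Patients in the comparator group will not be contacted during this year". Both arms attend T1 (4 months), T2 (1 year) and T3 (2 years).

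Assessing the safety of the intervention is a listed secondary objective. The Statistical analysis section evaluates safety endpoints in the full analysis set, by randomised arm. It states no between-arm test of adverse events.

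**The concern.** There are two separate problems.

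The first is classification. The SAE sentence is worded as a definition, not as examples, and the only admissions it covers are cardiovascular. In a trial of exercise, much of it done at home, an injury that leads to admission is a harm the safety report should be able to show as serious. As written, a fracture sustained in training is recorded only among the other events, next to a sore tendon. Life-threatening non-cardiovascular events that the patient survives are also outside the list.

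The second is ascertainment. Patients report the events, one arm meets staff far more often, and part of the non-serious wording presupposes an intervention that only that arm receives. If the counts are set side by side, some of any difference may reflect opportunity to report and not risk. The likely direction is more recorded events under PRIORITY. Minor events are most exposed; deaths and cardiovascular admissions are less so.

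**Working it through.** **SAE list, read against the recording rule.** The two sentences are adjacent. The first records and reports every adverse event under a Good Clinical Practice decision tree. The second limits serious events to three items. Applying the second to some examples:

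| Event | Serious under the stated list? |
|---|---|
| Death from any cause | Yes |
| Admission for cardiovascular disease | Yes |
| Serious atrial or ventricular arrhythmia | Yes |
| Admission for a fall, fracture or tendon rupture | No |
| Life-threatening non-cardiovascular event, survived | No |

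The last two rows are still recorded, but not as serious. The omission is the same in both arms.

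**Other-event wording, clause by clause.** Comparator patients receive an exercise prescription and may train as they wish, so a muscle or joint problem that precludes exercise can occur in either arm. An interruption of the exercise intervention can occur only in PRIORITY. One clause, not the whole category, is tied to one arm.

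**Contact count.** From the session schedule under Experimental group: PRIORITY intervention:

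- Month 1, weekly: 4
- Months 2–4, every two weeks: 2 × 3 = 6
- Months 5–12, monthly: 1 × 8 = 8
- Total: 4 + 6 + 8 = 18, which reproduces the stated 18 sessions.

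Adding the four consultations (months 12, 15, 18 and 21) gives 18 + 4 = 22 planned contacts beyond the shared visits, or 21 if the month-12 consultation coincides with T2. The comparator has 0. With T1–T3 included, the totals are 25 (or 24) against 3.

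**Recall at the shared visits.** T1 to T2 is 12 − 4 = 8 months; T2 to T3 is 24 − 12 = 12 months. For comparator patients these are the gaps between planned contacts.

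**Illustration only.** The protocol gives no event or detection rates, so these values are assumptions. Let the true risk p be the same in both arms, with detection s₁ in PRIORITY and s₀ in the comparator. Observed risks are p·s₁ and p·s₀, and the spurious risk ratio is s₁/s₀. The last column is the chance of a significant excess in PRIORITY, using a two-sided 5% test of two proportions with 156 per arm and no dropout.

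| True risk | s₁ | s₀ | Observed risks | Risk ratio | Chance of false significance |
|---|---|---|---|---|---|
| 10% | 0.9 | 0.8 | 9% v 8% | 1.12 | 5% |
| 20% | 0.9 | 0.6 | 18% v 12% | 1.50 | 32% |
| 30% | 0.9 | 0.5 | 27% v 15% | 1.80 | 74% |

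The outcome runs from negligible to serious depending on detection rates that nobody has stated. The table shows how the mechanism works; it does not estimate the bias in this trial.

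**The case against.** The case against is substantial, and much of it stands.

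- **One definition serves both arms.** A reader might infer that adverse events are defined differently by arm. The text does not support that: all events are to be recorded, and the other-event category is introduced by an inclusive verb, so it is not exhaustive. Only the interruption clause is specific to one arm.
- **No biased comparison is shown.** A reader might infer that the between-arm safety comparison is biased. The objective is to assess safety, no between-arm test is stated, and the analysis plan is not at hand. The comparator restriction bars contact for feedback or support, not the reporting of events. What can be said is that counts by arm are at risk.
- **Contacts are not detection.** The totals of 25 and 3 invite an 8:1 reading of detection. Nothing says that supervised sessions are event-collection points, and Table 3 shows reporting as continuous.
- **The SAE omission is symmetric.** It misclassifies events equally in both arms, so it is not itself a source of bias between them.
- **A shared source exists.** The Medical Consumption and Productivity Cost Questionnaires are scheduled for all patients at T0–T3, and the health economic section lists hospitalisation among the costs. This weakens the concern about admissions. However, the protocol does not link these data to safety, and they do not change what counts as serious.
- **The article condenses a fuller protocol**, which may hold more detailed procedures. That would excuse an omission, but the SAE definition is stated here in full.

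None of this widens the SAE list or shows that both arms are asked about events in the same way.

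**Conclusion.** The point holds in two parts.

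1. The SAE definition is a closed list without non-cardiovascular hospitalisation. An admission for a training injury would not be classed as serious in either arm. This follows from the wording alone and needs no assumption. It should be reconciled with the decision tree cited in the same section.
2. Adverse-event counts by arm are at risk of differential ascertainment, mainly for minor events. This rests on patient reporting, on one clause tied to the intervention, and on 21 to 22 extra planned contacts against none. It assumes that patients who meet staff more often report more. The size cannot be computed from the protocol.

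The primary efficacy analysis is unaffected. What is exposed is the listed safety objective. The change is worth making but is not critical.

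**What to change.** - **SAE definition.** Include death, life-threatening events and hospitalisation for any cause. Keep cardiovascular hospitalisation and serious arrhythmia as a separately reported subset. Reconcile the wording with the decision tree, and reclassify events already recorded.
- **Other events.** Replace the interruption clause with arm-neutral wording, for example any injury or illness that stopped usual physical activity.
- **Ascertainment.** Ask the same structured question in both arms at T1, T2 and T3, and base any between-arm summary on those visits. Report events noted at supervised sessions or consultations separately, for PRIORITY only.

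The visits already take place, so the direct cost is one question and revised wording. There are three downsides. SAE reporting increases somewhat. Because recruitment began in September 2021, some events will need retrospective reclassification, and some T1 visits may already have passed without the question. Relying on the shared visits also means 8 months of recall at T2 and 12 at T3, so some minor events will be missed in both arms.

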#### Other exploratory outcome measures

In a subsample, continuous wave *near-infrared spectroscopy* (NIRS, PortaMon, Artinis Medical systems, Elst, The Netherlands) measurements will be performed during the CPET to evaluate muscle oxygen saturation. NIRS relies on the light absorption properties of chromophores in the tissue of interest (e.g., hemoglobin and myoglobin in muscle). As the underlying myoglobin concentration tends to remain constant during exercise, the changes in the oxy- or deoxygenation signals can be attributed to changes in hemoglobin content (43, 44). In the same sample, *brachial artery vasoreactivity* will be evaluated by means of flow-mediated slowing (FMS), a technique that measures brachial pulse wave velocity deceleration to reactive hyperaemia via the brachial-radial oscillometric technique (Vicorder device, SMT medical technology GmbH, Würzburg, Germany) (45).

### Data management

Patient data will be anonymized using a personal identification code (PIC) on all case report forms and in the electronic database. Data will be recorded in hard copy at the time of the measurement and will subsequently be entered electronically in “REDCap (https://www.project-redcap.org)”, an open-source clinical trial software for electronic data capture and data management hosted at KU Leuven servers. Hard copies will be stored in a secured filing cabinet at the participating sites. Digital scans will be uploaded in the REDCap database and on the KU Leuven secure server. The type of activity that an individual user may undertake in the REDCap database is regulated by the privileges associated with his/her login credentials. Source data, randomization and pseudonymization lists are stored on a secure server of KU Leuven with password protection. All data analyses and reporting will be performed according to best practice and reported in agreement with Consolidated Standards of Reporting Trials guidelines (46). An independent researcher will regularly audit a randomly chosen subset of patients at each site to ensure adherence to the intervention program and the trial protocol. Any issues pertaining to nonadherence with the eligibility of a randomized participant, allocation of interventions, or concerns relating to adverse events are being discussed with and reviewed by the steering committee.

### Statistical analysis

The full analysis set (FAS) will, in accordance with the intent-to-treat principle, include all randomised patients according to their randomised treatment. The FAS will be used for the evaluation of all efficacy and safety endpoints. Patients from the FAS with major protocol deviations will be excluded from the per protocol set (PPS). A cLDA (18) model will be used to compare the pVO2 at 12 months between both groups. In this model, both the baseline pVO2 and post-baseline pVO2 values (4 months and at 12 months) are modelled as dependent variables, as opposed to a longitudinal ANCOVA model in which the baseline value is included as a covariate. The comparison at 12 months will be based on a two-sided test, setting alpha equal to 0.05. An unstructured covariance matrix will be used for the three longitudinal measurements. The HFpEF stage will be added as a factor in the model and the differences between the groups are allowed to differ between the stadia. The intervention effect will be calculated as a weighted average of the stage-specific effects. The estimation of the model will be likelihood based and results are therefore valid under the MAR (missing at random) assumption, i.e., subjects with a missing pVO2 value at a specific timepoint are assumed to be well represented by other subjects not having a missing value at that timepoint and having the same observed values at the other timepoints. Note that the comparison at 4 months, which will be derived from the same model, is a secondary outcome. The cLDA model (restricted to baseline and 12 months) will also be used for the comparison of the two key secondary outcomes, applying a Bonferroni-Holm correction.

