### Eligibility criteria and recruitment

The trial population will comprise 312 men and women (aged ≥30 years) along the continuum of HFpEF who are on optimal medical treatment and stable regarding symptoms and pharmacotherapy for at least 4 weeks before enrolment in the trial. All patients should have internet access at home. To represent the distribution of HFpEF stage A–C in the population, this will include 150 patients with HFpEF stage A, 90 patients with HFpEF stage B and 72 patients with HFpEF stage C. Participants will be recruited during a 2-year period which started in September 2021. Local investigators at each participating site will assess patient eligibility. A detailed description of the inclusion and exclusion criteria is shown in Table 1. Potentially eligible patients will then be contacted by a member of the research team and provided with a full oral explanation of the design and purpose of the trial, responsibilities of the participants, reasonably foreseeable inconveniences, and confidentiality of the information collected.

**Table 1 T1:** Inclusion and exclusion criteria for the PRIORITY trial.

HFpEF stage	Inclusion criteria	Exclusion criteria

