### Randomization and concealed allocation

Upon written informed consent and following the baseline measurements including a fasting blood draw, cardiopulmonary exercise test (CPET) and a rest and exercise echocardiography, patients will be randomized to either the PRIORITY group or the comparator group with a 1:1 allocation ratio stratified by HFpEF stage, as shown in Table 1. Asymptomatic patients with HF risk factors such as hypertension, (pre)diabetes, and obesity but free from echocardiographic abnormalities will be classified as stage A. Early HF phenotypes (stage B) will be defined as asymptomatic patients with HF risk factors and echocardiographic evidence of cardiac structural and functional abnormalities, consistent with the presence of left ventricular diastolic dysfunction and/or raised left ventricular filling pressures as defined by 2 out of 4 ESC criteria (Table 2) (16). Patients with symptomatic HF (stage C) will be characterized as symptomatic patients with an HFA-PEFF score of ≥5 (4). For patients with an intermediate HFA-PEFF score after resting echocardiography, the results of the diastolic stress test will be included in the score [i.e., average *E*/*e*′ ≥15 adds 2 points and an average *E*/*e*′ ratio ≥15 with a peak tricuspid regurgitation (TR) velocity >3.4 m/s adds 3 points to the previous score after the resting echocardiography]. Randomization schedules are generated using a computerized random number generator. Randomization is being performed by an independent designated member of the coordinating centre (KU Leuven) in response to a request from a local investigator, thus assuring concealed allocation and minimizing selection bias.

**Table 2 T2:** Objective evidence of cardiac structural or functional abnormalities consistent with the presence of left ventricular diastolic dysfunction/increased left ventricular filling pressures.

Parameter	Threshold
LV mass index (LVMI)	≥95 g/m^2^ (♀), ≥115 g/m^2^ (♂)
or Relative wall thickness (RWT)	>0.42
LA volume index (LAVI)	>34 ml/m^2^ (SR), >40 ml/m^2^ (SR)
Average (septal and lateral) *E*/*e*′ ratio at rest	>9
Estimated PA systolic pressure	>35 mmHg
TR velocity at rest	>2.8 m/s

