### Sample size calculation

The power calculation is based on a constrained longitudinal data analysis (cLDA) model (17, 18) and calculated using an approach presented by Stroup (19). To have at least 90% power to detect a difference of 2.7 ml/kg/min in pVO2 after 12 months, 90 subjects per group (180 in total) are required based on a two-sided test and setting alpha equal to 0.05. The effect size of 2.7 is a weighted average of the expected effects in the three stages i.e., 0.20 × 1 ml/kg/min (Stage C) (20, 21) +0.30 × 2.5 ml/kg/min (Stage B) +0.50 × 3.5 ml/kg/min (Stage A) (22, 23). A common standard deviation of 5, a correlation between baseline and 12 months equal to 0.50 and a drop-out rate at 12 months as high as 40% were assumed (24). However, the sample size will be increased to 312 patients in total (156 per group) such that for two key secondary outcomes standardized effect sizes as small as 0.45 and 0.40 can be detected with more than 90% and 80% power, respectively (using a cLDA model assuming—as for the primary outcome—a baseline-year correlation of 0.50% and 40% dropout at 12 months). For example, for the key secondary outcome (moderate to vigorous physical activity, MVPA) a standardized mean difference equal to 0.42 corresponds to a difference of 1,235 steps (25). Note that for the power calculation of the key-secondary outcomes an alpha-level of 0.05/2 = 0.025 was used.

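### The pVO2 model is valid, but prespecifying baseline age and sex as covariates would add modest precision and some protection against differential dropout at almost no cost

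*Protocol article*

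**What the plan says.** The Statistical analysis section describes the primary model in some detail. In the cLDA, "both the baseline pVO2 and post-baseline pVO2 values (4 months and at 12 months) are modelled as dependent variables". On covariance: "An unstructured covariance matrix will be used for the three longitudinal measurements". On covariates: "The HFpEF stage will be added as a factor in the model", with group effects free to vary from stage to stage. The overall effect is then a weighted average of the stage-specific effects. No age, sex or other baseline covariate is named.

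Missing data are handled by likelihood under MAR. The article explains this as patients with a missing value being represented by others "having the same observed values at the other timepoints". The two key secondary outcomes (daily steps and MVPA) get the same type of model, restricted to baseline and 12 months.

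Three other places bear on the point:
- Randomization and concealed allocation: allocation is "with a 1:1 allocation ratio stratified by HFpEF stage", so the only named stratification factor is already in the model.
- Eligibility criteria and recruitment: "The trial population will comprise 312 men and women (aged ≥30 years) along the continuum of HFpEF".
- Sample size calculation: SD 5, baseline to 12-month correlation 0.50, and "a drop-out rate at 12 months as high as 40% were assumed".

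**The concern.** With both sexes and an open-ended adult age range, age and sex may explain a worthwhile part of the between-patient variation in pVO2. At an assumed correlation of 0.50, baseline pVO2 leaves 75% of the 12-month variance unexplained. Part of that remainder could be removed by two variables that need no new measurement. Leaving them out may give a wider interval than the data allow.

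The same two variables are absent from the information on which the MAR assumption is conditioned. If they are related to dropout in one arm more than the other, and still predict the 12-month value after stage and the observed outcome values, the treatment contrast could be biased.

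The article does not list age and sex by name as recorded variables, but the inference is safe. Eligibility has a minimum age, Table 2 has sex-specific thresholds for LV mass index, and Table 3 schedules a sociodemographic questionnaire at baseline.

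**Working it through.** **1. Reproduce the plan's figure.** Inputs from the Sample size calculation section: difference 2.7 ml/kg/min, SD 5, correlation 0.50, two-sided alpha 0.05, power 90%, dropout 40%.

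- Residual SD given baseline: 5 × √(1 − 0.50²) = 4.33.
- Completers per arm: 2 × (4.33 × (1.960 + 1.282) / 2.7)² = 54.05.
- Randomised per arm: 54.05 / 0.6 = 90.1. The plan states 90, so it reproduces.

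**2. Position at the actual size.** With 156 per arm and 40% dropout there are 93.6 completers per arm.

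- SE = 4.33 × √(2 / 93.6) = 0.633 ml/kg/min; 95% half-width 1.24.
- Power for 2.7 ml/kg/min: 98.9%.
- Key secondary outcomes at alpha 0.025: 90.5% for a standardised effect of 0.45 and 82.1% for 0.40. Both agree with the plan.

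**3. Precision gain for pVO2.** The document does not say how much pVO2 variance age and sex explain. Let that share be R² (assumption), with effects stable over time, and let ρ be the baseline to 12-month correlation. As a fraction of total variance:

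- residual given baseline pVO2: 1 − ρ²
- residual given baseline pVO2, age and sex: (1 − R²) − (ρ − R²)² / (1 − R²)

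For ρ = 0.50 and R² = 0.3: 0.75 falls to 0.70 − 0.04/0.70 = 0.643. The ratio is 0.857, so the SE is multiplied by √0.857 = 0.926.

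| Assumed R² | Partial R² beyond baseline, ρ 0.50 | SE reduction, ρ 0.50 | SE at N = 312, ρ 0.50 | SE reduction, ρ 0.85 |
|---|---|---|---|---|
| 0.1 | 0.037 | 1.9% | 0.621 | 0.5% |
| 0.2 | 0.083 | 4.3% | 0.606 | 1.0% |
| 0.3 | 0.143 | 7.4% | 0.586 | 1.8% |
| 0.4 | 0.222 | 11.8% | 0.558 | 2.7% |

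At R² = 0.3 and ρ = 0.50, primary power moves from 98.9% to about 99.6%. The calculation leaves out stage and the 4-month value, both already in the model, so the real gain for pVO2 may be smaller.

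**4. Key secondary outcomes.** For a standardised effect of 0.40 at alpha 0.025, SE = √(0.75 × (1 − partial R²)) × √(2 / 93.6), and power = Φ(0.40 / SE − 2.241). For an assumed partial R² of 0, 0.05, 0.10 and 0.143, power is 82%, 84%, 86% and 88%.

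**5. Dropout.** A large-sample simulation used baseline and 12-month values with SD 5, correlation 0.50, effect 2.7 and about 40% dropout. Retention depended on an age–sex score (log-odds 0.5 per SD), with R² from 0.1 to 0.3. All of these settings for the score are assumptions. Bias in the treatment difference, in ml/kg/min:

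| Dependence of dropout on the score | Score left out | Score included |
|---|---|---|
| Same in both arms | about 0 | about 0 |
| One arm only | 0.16 to 0.28 | about 0 |
| Opposite directions by arm | 0.30 to 0.55 | about 0 |

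**The case against.** The strongest reply is that nothing here is wrong. The model contains the only named stratification factor, uses baseline pVO2 efficiently, and fixes its covariance, contrast and missing-data assumption. Further prognostic covariates are often left to a statistical analysis plan, which is not shown and may already include them. All of this stands, and it is why the point is put as an improvement to a stated model and not as a defect.

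The size is also open to challenge. R² is assumed, and any variance that age and sex share with stage is no gain. The larger gains also pair a low correlation with a high R². After removing age and sex, the baseline to 12-month correlation would be (0.50 − 0.3)/0.7 = 0.29, or 0.17 at R² = 0.4. That would make pVO2 barely reproducible within a patient. So the upper end of the range deserves little weight. Nor does the document give an R² for steps or MVPA, so the gain for those outcomes is purely conditional.

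A reader might go further on four points, and the document does not support them:
- **That MAR holds only if dropout is unrelated to age and sex.** It also holds if they do not predict 12-month pVO2 given stage and the observed pVO2 values.
- **That the planned estimate is biased.** Bias in the contrast needs residual prediction and arm-differential dropout together. The arms do differ in contact: 18 supervised sessions against no first-year contact beyond the 4-month assessment. That makes differential dropout conceivable but does not show it.
- **That 40% of 12-month values will be missing.** It is a planning ceiling.
- **That primary power is at risk.** It is about 99%.

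**Conclusion.** The point holds as a low-cost improvement. The planned cLDA is valid and the design figures checked here reproduce. The stated model uses no baseline predictor besides stage and the outcome's own baseline value, although age and sex are evidently available in a population with a wide age range.

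For an age–sex R² of 0.1 to 0.4, the SE for pVO2 falls by roughly 2–12% at a correlation of 0.50 and 0.5–3% at 0.85. The lower part of each range is the more credible. The practical benefit is a somewhat narrower primary interval and, if the assumed partial R² of 0.05–0.14 carries over to the key secondary outcomes, a few points of power for an effect of 0.40. Protection against arm-differential dropout by age or sex is a further, contingent benefit.

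**What to change.** In the Statistical analysis section, and in the statistical analysis plan if it does not already say so, prespecify baseline age (continuous) and sex, each with visit-specific coefficients, as covariates in the cLDA for pVO2 and in the models for steps and MVPA. Leave the stage-specific group effects, their weighted average and the 12-month contrast as they are. Make the change before unblinding. If the analysis plan already contains these covariates, align the article's description with it.

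The cost is a few degrees of freedom and one sentence of text. No new data are needed.
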